## Abstract

Chronic Obstructive Pulmonary Disease (COPD) is a major cause of morbidity and mortality in the United States and is a growing cause of chronic disease internationally. Presently, there are limited treatment options for this disease to modify the progression of airflow obstruction and decrease periodic exacerbations. Recent evidence has emphasized the central role of oxidative stress as a mechanism of COPD pathobiology. Evidence from our group has shown that COPD patients and animals exposed to cigarette smoke have impairment of antioxidant defenses which are caused by a defect in activity of Nrf2, a prolific regulator of anti-oxidant enzymes, glutathione homeostasis, and cytoprotective proteins. Activation of Nrf2 protects mice with chronic smoke exposure from developing emphysema, decreases oxidative stress, increases proteasomal anti-apoptotic cytoprotective responses, improves bacterial phagocytosis and killing, and reverses tobacco-smoke induced corticosteroid resistance. Similarly, *in vitro* Nrf2 activation in human COPD lung cells has shown improved cytoprotection, improved bacterial clearance, and restoration of steroid sensitivity. This trial focuses on sulforaphane, a derivative of cruciferous vegetables, which is a potent *in vitro* and *in vivo* stimulator of Nrf2 activity. We want to investigate whether ingestion of sulforaphane by COPD patients will increase Nrf2 activity and expression of downstream antioxidants in alveolar macrophages and bronchial epithelial cells. Accordingly, we are conducting a placebo-controlled randomized proof of principle trial of two oral doses of sulforaphane, 25 and 150 micromoles, for 4 weeks in 90 COPD patients. Collections of alveolar macrophages by BAL, bronchial epithelial cells by endobronchial brushings will be performed at baseline and 4 weeks. Other biospecimens will include nasal epithelial cells, Peripheral Blood Monocyte Collection (PBMCs), and expired breath condensate (EBC). Our goal is to establish a safe and tolerable dose of sulforaphane that effects *in vivo* antioxidants via Nrf2, then we will have a novel candidate treatment for longer-term efficacy trials. Ancillary studies are proposed to explore the efficacy and mechanisms of sulforaphane to increase bacterial clearance and to restore steroid sensitivity in COPD lung cells.

## 1. Introduction

### 1.1 Title

Broccoli Sprout Extracts Trial (BEST)

### 1.2 Sponsors

National Institutes of Health/National Heart Lung Blood Institute U01 HL105569-01 ([name] and [name])

### 1.4 Background and Significance

Chronic Obstructive Pulmonary Disease (COPD) is a highly morbid disease, mainly caused by cigarette smoking in the United States, afflicting 24 million people. More than 125,000 people die from COPD each year, making it the fourth leading cause of death in the U.S. The total costs for COPD care are estimated to be \$29 billion per year.

#### Current Treatments for COPD

Despite the rising morbidity and mortality, there are few new treatments that can arrest the progress of the disease. Drug treatment relies largely on bronchodilators and inhaled corticosteroids, which improve lung function and reduce exacerbations but have limited effect on progression of the disease. Aside from smoking cessation, there are no treatments that directly address the underlying pathobiology of COPD.

#### Role of bacterial exacerbations in COPD

Patients with COPD have, on average, 1-3 exacerbations per year, but the frequency varies widely among patients. Exacerbations are associated with faster loss of lung function, impaired quality of life, increased mortality, and greater costs of healthcare. An estimated 10% of patients with frequent and severe exacerbations account for 70% of the total health care use. Risk factors include the presence of cough and mucus, and colonization of the lower airways by bacteria. Approximately 50% of exacerbations are due to bacterial infections, most frequently non-typeable H. Influenza. A major goal of COPD treatment is to reduce exacerbations.

### Disease Modification in COPD

Although treatment moderately reduces the frequency of exacerbations and improves lung function, there are no treatments that clearly alter the progression of the disease through interruption of the chronic inflammatory processes that lead to parenchymal destruction and airway remodeling. Thus, there is a need for new approaches to therapy that can address directly the pathobiologic alterations that occur in COPD.

### Pathobiology of COPD

Only a minority of smokers develop clinically important COPD. In recent years, our understanding of the pathobiology of COPD has increased considerably. Among other key findings, we now know that patients with COPD, in contrast to smokers without COPD have the following characteristics.

- Increased burden of oxidative stress and impaired anti-oxidant defenses.
- Impaired macrophage function including phagocytosis and bacterial killing.
- Resistance to the anti-inflammatory effects of corticosteroids.
- Persistent pulmonary and systemic inflammatory response.

These phenomena account for some of the clinical characteristics of COPD including:

- the progression of disease in some individuals after smoking cessation
- the frequency of bacterial infections causing exacerbations of disease
- the relative ineffectiveness of inhaled steroids in COPD compared to asthma

### Oxidative stress in COPD

There is a growing body of evidence that oxidative stress plays a pivotal role in the development and maintenance of the inflammatory response in COPD. Increased oxidative stress has been found in biological samples from the bronchial lavage, expired breath, blood, and urine in patients with COPD compared to smokers without COPD and non-smokers. The consequences of oxidative stress include: 1) inactivation of antiproteases, 2) down regulation of HDAC2 causing steroid insensitivity, 3) alveolar epithelial injury and apoptosis 4) gene expression of inflammatory mediators. 4) Oxidative stress may stimulate mucus secretion and impair mucociliary clearance. 5) Decrease alveolar macrophage bacterial killing. Accordingly, it is logical to target oxidative stress as a promoter of the clinical manifestations of COPD including parenchymal destruction of the lung and recurrent exacerbations.

### Failure of Nrf2 – a unifying pathway to COPD

[name]'s laboratory has focused on the role of *Nuclear factor erythroid 2-related factor 2* (Nrf2) in the pathogenesis of COPD. Nrf2 is a prolific transcription factor, induced by oxidative stress, that binds to the antioxidant response element (ARE) and induces a broad program of antioxidant enzymes, glutathione homeostasis, and detoxification enzymes including anti-proteases. Moreover, we have recently demonstrated that COPD patients are deficient in Nrf2.

### Preliminary Data

Key preliminary findings from the [name] laboratory have shown the following:

- In tobacco-exposed mice, Nrf2 protects from cigarette smoke induced oxidative injury and emphysema.
- In tobacco-exposed mice, Nrf2 activation by genetic disruption of Keap1 protects from cigarette-smoke induced lung injury
- In tobacco exposed mice, pharmacological activation of Nrf2 by sulforaphane and other small molecules protects from CS-induced oxidative lung injury and emphysema

- In lung tissues from humans with COPD, decline in Nrf2 and Nrf2-regulated cytoprotective defenses in lungs correlates with severity of COPD
- In mouse lungs, in-vivo treatment with sulforaphane upregulates Nrf2-directed cytoprotective defenses.
- In human bronchial epithelial cell lines, in-vitro treatment with sulforaphane upregulates Nrf2-directed antioxidant and cytoprotective defenses.
- Sulforaphane treatment inhibits bacterial colonization in CS exposed Nrf2+/+ mice but not in Nrf2-/- knockout mice (preliminary data)
- Sulforaphane treatment in-vitro improves bacterial phagocytosis in COPD alveolar macrophages via Nrf2 mediated increase in surface receptor MARCO (Preliminary data)
- Sulforaphane treatment in-vitro improves corticosteroid protection in COPD alveolar macrophages exposed to LPS (preliminary data)

Thus, it appears that reduction in Nrf2 can account for many of the observed defects in COPD, and that treatments that stimulate the production of Nrf2 is a logical approach to treatment of the disease with a goal of disease modification – slowing of parenchymal destruction and resistance to bacterial exacerbations.

Antioxidant strategies for COPD Trials of supplemental antioxidants using NAC and vitamin E show modest or no effect on FEV1 decline. This failure may be attributed to the fact that these single antioxidant molecules gave insufficient protection at the lung tissue level or may have been given in insufficient dose to affect susceptible tissues. On the other hand, a novel strategy based on targeting Nrf2, which up-regulates a broad range of cytoprotective genes including antioxidants is a much more promising therapy as evidenced in the preclinical data.

Nrf2 Activators Several compounds are effective in increasing Nrf2 in preclinical models. These include dithiolethiones, sulforaphane, the triterpenoid CDDO, resveratrol, curcumin, and quercetin. Among these sulforaphane is the most extensively studied in humans and has the most relevant pre-clinical support for use in COPD. Sulforaphane is an isothiocyanate that is derived from mastication of cruciferous vegetables which converts the glucosinolate form to the active compound. Sulforaphane has several demonstrated properties that suggest that it would be an ideal treatment for COPD.

- It stimulates Nrf2 and downstream anti-oxidants, proteasomal subunits and other cytoprotective genes in lung tissue
- It reduces ER stress that leads to apoptotic cell death in tobacco exposed lungs
- It confers increased activity to macrophages to phagocytose and kill bacteria that cause COPD exacerbations in tobacco exposed mouse lungs and human COPD macrophages. (see ancillary study 1)
- It reduces oxidative / nitrosative modifications of critical proteins such as HDAC2 that mediate corticosteroid anti-inflammatory resistance in COPD (see ancillary study 2)

#### Other biological effects of sulforaphane

In pre-clinical studies, sulforaphane has a number of other potentially beneficial effects that may confer benefit to COPD patients with respect to co-morbid conditions such as lung cancer, arteriosclerosis, and respiratory viral infections.

- Sulforaphane suppresses endotoxin-induced inflammatory response by inhibiting TLR4 and NF-KB signaling
- Sulforaphane inhibits lung RSV replication and virus-induced inflammation in mice

- Sulforaphane suppresses inflammatory responses in endothelial cells and arterial damage induced by shear stress
- Sulforaphane suppresses T-cell activation and protects from arthritis in mice
- Sulforaphane protects from ischemic injury of the heart through oxidative stress
- Dietary sulforaphane protects against hypertension and atherosclerosis by reducing oxidative stress
- Sulforaphane confers neuroprotection in endotoxin, cerebral hemorrhage and trauma by suppressing inflammation and oxidative stress.
- Sulforaphane protects against inflammatory skin disorders including UV induced skin injury and epidermolysis bullosa
- Sulforaphane exhibits anti-bacterial activity against *Helicobacter pylori* and prevents benzopyrene-induced stomach tumors
- Sulforaphane inhibits malignant progression of lung adenomas induced by tobacco carcinogen in mice as well as anticancer properties in other organs

### **Potential Impact of the Proposed Research**

If we are able to demonstrate that orally administer sulforaphane has similar biological properties as it has *in-vivo* in experimental animals exposed to tobacco and *in-vitro* to human COPD lung cells, this will provide us with an agent that can be readily developed to be taken into Phase III trials. It would suggest that sulforaphane would be effective not only in limiting the progression of COPD, but also decrease the frequency and severity of exacerbations. The clinical importance of developing a drug that can effectively modify the progression of COPD would not only alleviate suffering and reduce healthcare expenditures, but would address what is arguably the most significant unmet need in pulmonary medicine in the world. We are also optimistic that sulforaphane has potential for distribution not only as a drug, but also in the form of nutritional supplementation or dietary modification which would make it accessible to vast numbers of individuals in third-world countries where COPD is a growing problem.

### **1.5 Objectives**

The primary goals of this trial are to:

- Establish proof of principle -- Does oral sulforaphane increase Nrf2 expression and downstream anti-oxidant enzymes in lung macrophages and epithelial cells.
- Determine tolerability and dose-ranging for subsequent clinical research
- Establish non-invasive surrogate biomarkers for Nrf2 expression in the lung
- Conduct ancillary mechanistic studies to determine whether *in-vivo* treatment increases bacterial phagocytosis and killing and decreases corticosteroid resistance

## **2. Study design**

### **2.1 Hypotheses**

Daily ingestion of 25 or 150 micromoles of sulforaphane for 4 weeks will have the following dose-dependent effects:

- H1. Increase Nrf2 activation in alveolar macrophages and bronchial epithelial cells
- H2. Increase phase II anti-oxidant enzymes in alveolar macrophages and bronchial epithelial cells
- H3. Reduce markers of oxidative stress in expired breath condensate
- H4. Increase bacterial clearance of clinical isolates of *Haemophilus influenza* and *Pseudomonas aeruginosa* from COPD patient by alveolar macrophages. (Ancillary Study 1)
- H5. Increase steroid (dexamethasone) sensitivity to suppression of IL8 release by LPS in alveolar macrophages. (Ancillary Study 2)

Exploratory studies will be done to determine whether sulforaphane has lung anti-inflammatory properties and whether non-invasively collected specimens (blood and nasal brushings) can be used as surrogates for response of lung cells.

## 2.2 Trial Schema

The trial will be a 3-arm parallel design randomized placebo-controlled trial in 90 COPD patients. After screening (V1), participants are scheduled for a baseline clinical evaluation (V2) and a bronchoscopy (V3) within a week. The clinical evaluation (V4) and bronchoscopy (V5) are repeated 4 weeks later. Although the effects of sulforaphane on nasal epithelium are known to occur within several days, the 4 week treatment period is long enough to permit the inflammatory response from the first procedure to subside and to provide an assessment of tolerability of the treatment.

[figure not shown]

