#### **2.5.1 Primary outcome**

1. Nrf2 levels and downstream anti-oxidants The primary design variables are the change in Nrf2 expression in alveolar macrophages (AM) and bronchial epithelial cells (BEC). Support of antioxidant effects will be quantified by changes in phase II anti-oxidant gene expression (NQO1, HO-1, GPX2, GCLM, GCLC, GSTA1). We will correlate changes in these levels with non-invasive measures from peripheral blood monocytes and nasal epithelial cells.

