## 2.6 Study Data Collection schedule

The specific study procedures and approximate time commitment from the participant are shown below:

Participants will have 5 study visits over 4-8 weeks as follows:

Visit 1 (V1) (Day – 28 to -7) (2 hours) During this visit, the participant will provide informed consent, undergo eligibility screening questionnaire, lung function (spirometry before and after bronchodilators), Complete Blood Count, biochemistry panel including renal and liver function and electrolytes, TSH, urinalysis, and a pregnancy test for women of child-bearing potential.

Visit 2 (V2) (Day -14 to 0) (2-4 hours) During this visit, eligible participants will perform baseline spirometry, lung volumes, and diffusing capacity, and will complete general health questionnaires and respiratory specific questionnaires (ATS-DLD, SGRQ and MRC). A brief physical examination will be performed. Baseline biological specimens including blood for PBMCs will be performed.

Visit 3 (V3) (Day 0) (4 hours) The participant will have a baseline bronchoscopy for collection of bronchoalveolar lavage cells and nasal and bronchial epithelial brushings. Randomization eligibility will be established and the participant will be assigned to a masked treatment. After recovery from the bronchoscopy sedation, the participant will be given the assigned treatment which will consist of a coded container of capsules containing either placebo or one of the two doses of sulforaphane.

Phone Visit 1 (P1) (Day 1) (15-30 minutes) Patients are phoned the day following the bronchoscopy to determine whether they have had any adverse experiences, to re-instruct them in use of the medication, and to confirm future appointment dates and times.

Phone Visit 2 (P2) (Day 7-14) (15-30 minutes) Patients are contacted to determine their compliance with the medication and to report any adverse effects.

Visit 4 (V4) (Day 21 to 30) (2 – 4 hours) The participant will repeat the baseline spirometry, lung volumes and diffusion capacity, CBC, pregnancy test, urinalysis, TSH and biochemistry panel and have follow-up health status and adverse effect questionnaires and a brief physical examination. Follow-up collections of blood for biological measures are obtained.

Visit 5 (V5) (Day 22 to 31) (4 hours) Follow-up bronchoscopy for collection of bronchoalveolar lavage, nasal brushings, specimens and endobronchial brushings. Return of unused capsules for pill counts.

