**Table 1: Study Data Collection Schedule**

| Visit                           | V1        | V2       | V3 | P1 | P2   | V4    | V5    | P3    |
|---------------------------------|-----------|----------|----|----|------|-------|-------|-------|
| Time window (days)              | -28 to -7 | -14 to 0 | 0  | 1  | 7-14 | 21-30 | 22-31 | 24-38 |
| Target (days)                   | -21       | -14      | 0  | 1  | 14   | 25    | 26    | 27    |
| Consent, eligibility evaluation | •         |          |    |    |      |       |       |       |
| Screening Questionnaire         | •         |          |    |    |      |       |       |       |
| Spirometry/PFTs                 | •         | •        |    |    |      | •     |       |       |
| Pulse Oximetry                  | •         | •        |    |    |      |       |       |       |
| Lung volume/DCO                 |           | •        |    |    |      | •     |       |       |
| CBC, Chemistry panel, TSH       | •         |          |    |    |      | •     |       |       |
| Urine analysis                  | •         |          |    |    |      | •     |       |       |
| Physical Exam                   |           | •        |    |    |      | •     |       |       |
| Pregnancy Test                  | •         |          |    |    |      | •     |       |       |
| Randomization                   |           |          | •  |    |      |       |       |       |
| Health Status / AE              |           | •        |    |    |      | •     |       |       |
| SGRQ/MRC                        |           | •        |    |    |      | •     |       |       |
| ATS-DLD                         |           | •        |    |    |      |       |       |       |
| EBC                             |           | •        |    |    |      | •     |       |       |
| PBMC/Plasma/Serum               |           | •        |    |    |      | •     |       |       |
| Nasal Brush                     |           |          | •  |    |      |       | •     |       |
| BAL/Bronchial Brush             |           |          | •  |    |      |       | •     |       |
| Adherence Counseling            |           |          |    | •  | •    |       |       |       |
| Exit interview                  |           |          |    |    |      |       |       | •     |

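### Table 1 targets the baseline blood sample 14 days before the baseline bronchoscopy, against within a week in section 2.2 and a one-day gap at follow-up, which can weaken the blood-lung correlation of changes for reasons of timing

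*Protocol*

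**What the plan says.** Protocol section 2.2 (Trial Schema) says of the baseline visits that "participants are scheduled for a baseline clinical evaluation (V2) and a bronchoscopy (V3) within a week", and of follow-up that "The clinical evaluation (V4) and bronchoscopy (V5) are repeated 4 weeks later".

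Section 2.6 opens its V2 entry with "Visit 2 (V2) (Day -14 to 0) (2-4 hours", and Table 1 repeats that window. The target row of Table 1, in the order V1, V2, V3, P1, P2, V4, V5, P3, reads "Target (days) | -21 | -14 | 0 | 1 | 14 | 25 | 26 | 27". The follow-up windows are day 21 to 30 for V4 and day 22 to 31 for V5.

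On sampling, the V2 entry states that "Baseline biological specimens including blood for PBMCs will be performed". Table 1 puts PBMC, plasma, serum and breath condensate at V2 and V4. It puts nasal brushings, BAL and bronchial brushings together at V3 and V5.

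On use, section 2.5.1 says of the lung-cell measures: "We will correlate changes in these levels with non-invasive measures from peripheral blood monocytes and nasal epithelial cells". Finding non-invasive surrogates is among the primary goals in section 1.5. Section 2.1 describes the same work as exploratory.

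**The concern.** A site that meets the V2 target exactly leaves two weeks, not one, between the baseline clinical evaluation and the baseline bronchoscopy. The same pair of visits at follow-up is targeted one day apart. The protocol gives no reason for the difference.

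The two candidate surrogates are therefore not measured on equal terms. The nasal change is taken over the same days as the lung change. At target, the blood change starts 14 days earlier, so it contains two weeks of spontaneous variation that the lung change does not share. If the marker drifts within a patient over two weeks, the blood-lung correlation falls even when blood tracks the lung as well as the nose does. A reader who sets the two correlations side by side could take a scheduling effect for a biological one.

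**Working it through.** **Step 1: day counts.** Inputs are the targets and windows in section 2.6 and Table 1.

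| Interval | At target | Range allowed by windows |
|---|---|---|
| V2 to V3 (blood to lung, baseline) | 0 - (-14) = 14 days | 0 to 14 |
| V4 to V5 (blood to lung, follow-up) | 26 - 25 = 1 day | 0 to 10 |
| V2 to V4 (span of blood change) | 25 - (-14) = 39 days | 21 to 44 |
| V3 to V5 (span of lung and nasal change) | 26 - 0 = 26 days | 22 to 31 |
| V1 to V3 | 0 - (-21) = 21 days | 7 to 28 |

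Section 2.2 implies at most 7 days for V2 to V3; the targets give 14. If the phrase is read instead as a week from screening, V1 to V3 is 21 days at target, so the conflict remains. The repeat of the clinical evaluation after four weeks (28 days) is likewise not met at target, where V2 to V4 is 39 days.

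**Step 2: what the offset could do to the correlation.** The protocol gives no within-patient variability, so this step rests on assumptions. Suppose blood and lung share one fluctuating signal with autocorrelation φ(d) = exp(-d/τ) at a lag of d days, and both share a treatment response with SD s, in units of the fluctuation SD. At target, the fraction of the same-day correlation of changes that survives is

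[φ(1) + φ(14) - φ(40) - φ(25) + s²] / √{(2[1 - φ(26)] + s²)(2[1 - φ(39)] + s²)}.

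The lags are V4-V5 = 1, V2-V3 = 14, V2-V5 = 40, V3-V4 = 25, V3-V5 = 26 and V2-V4 = 39.

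For τ = 14 and s = 0:

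- numerator: 0.931 + 0.368 - 0.057 - 0.168 = 1.074
- denominator: √(1.688 × 1.877) = 1.780
- ratio: 0.60

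For s = 1 the ratio is 2.074 / √(2.688 × 2.877) = 0.75. For s = 2 it is 5.074 / √(5.688 × 5.877) = 0.88.

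| τ (days) | s = 0 | s = 1 | s = 2 | s = 0, V2 at day -7 | s = 0, V2 at day -1 |
|---|---|---|---|---|---|
| 7 | 0.49 | 0.66 | 0.83 | 0.61 | 0.86 |
| 14 | 0.60 | 0.75 | 0.88 | 0.73 | 0.92 |
| 30 | 0.69 | 0.82 | 0.92 | 0.80 | 0.94 |
| 60 | 0.74 | 0.88 | 0.95 | 0.84 | 0.95 |

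The nasal sample has no offset at either end, so its fraction is 1 throughout. Moving V2 to day -7 would satisfy section 2.2 but recover only part of the loss. Matching the one-day follow-up gap recovers most of it.

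**The case against.** The strongest reply is that the conflict sits in one target cell. The V2 window of day -14 to 0 lets a site do V2 within a week of V3, or on the same day, without a deviation. The follow-up windows allow a gap of up to 10 days, so the actual asymmetry may be smaller than 14 against 1. This stands. The 14-day lead and the 39-day span are target values, and every fraction in the table assumes that all patients are seen on target.

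Second, the surrogates are meant to follow response to treatment. Both baseline samples are pre-dose and both follow-up samples fall in the treatment period, so a shared response is not lost through the baseline lag. This also stands, and it is why the columns for s = 1 and s = 2 belong beside s = 0.

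Three stronger readings are tempting but unsupported:

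- **Blood will be discarded in favour of nose.** Section 2.5.1 only correlates each with lung. The protocol has no head-to-head test, ranking or selection rule. Section 2.1 calls the work exploratory, and the proof-of-principle criterion in section 2.5 does not use the surrogates.
- **The treatment comparison is biased, including breath condensate for H3.** The schedule is the same in all arms, so the early baseline adds at most noise. Breath condensate is also not one of the surrogates named in section 2.1.
- **About half the correlation is lost.** That is the case of short memory and no shared response, not a figure from the protocol.

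**Conclusion.** The inconsistency is certain: section 2.2 and the Table 1 targets cannot both be followed. So is the asymmetry at target, with blood leading lung by 14 days at baseline and 1 day at follow-up, and nose and lung concurrent at both.

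The direction of the consequence follows from the schedule: the blood-lung correlation of changes can only be put at a disadvantage to the nose-lung one. Its size is unknown. Under the assumed model with τ of 7 to 60 days, 49-74% of the same-day correlation survives with no shared response, 66-88% with a response SD of one fluctuation SD, and 83-95% with two. The loss is small where markers are stable over two weeks and the observed changes mainly reflect a shared response.

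This is worth correcting because the surrogate question is a listed goal and a baseline sample nearer in time to the lung sample cannot be recovered afterwards. It does not threaten the randomised comparisons.

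**What to change.** Reconcile section 2.2, the visit entries in section 2.6 and Table 1. Set the V2 target, and preferably narrow its window, so that the V2-V3 gap is at most a week and matches the V4-V5 gap. A target of day -1 would do both: the blood-lung offset becomes 1 day at each end, and the blood change spans 25 - (-1) = 26 days, equal to the lung change.

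Taking the research blood on the bronchoscopy days (V3 and V5) would remove the offset altogether. It is optional, goes further than the inconsistency requires, and would add sample processing to days that already involve fresh-cell work for the ancillary studies.

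The main edit needs no added visit, procedure or blood. Its cost is slightly tighter scheduling before the baseline bronchoscopy.
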